### Sensitivity and additional analyses

Dependent on the number of HCWs and events captured, we intend to conduct the following additional analyses:

*Incorporating BMI and smoking into broad analysis*: adjust for BMI and smoking in COVID-19 outcome models if recorded by EHRs either during, or in the 24 months prior to, the study period.
*Incorporating grouping by organisation*: incorporate clustering of HCWs within organisations by fitting hierarchical models to account for within organisation correlation and between organisation heterogeneity.
*Granular analysis within the ‘Asian/Asian British’* ethnicity category: investigate differences in COVID-19 outcomes between HCWs with South Asian (Indian, Pakistani and Bangladeshi), East Asian (Chinese) and Other Asian backgrounds.Granular analysis within the “medical staff” occupational group: investigate differences in COVID-19 outcomes between medical and dental subcategories.Subgroup analysis within hospital workers: investigate COVID-19 outcomes in hospital workers and cluster HCWs within hospitals using hierarchical models.
*Subgroup analysis of ancillary workers*: investigate COVID-19 outcomes in ancillary workers through trusts that employ them directly.
*Missing ethnicity*: explore approaches to deal with missing ethnicity information.
*Missing data*: use multiple imputation to assess the robustness of our findings to missing data.

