### Predictors

We will investigate and adjust for the following core predictors: age, sex, comorbidities and socioeconomic deprivation. A description of the definitions for these core predictors, and how they will be assessed, is provided in table 4.

**Table 4 T4:** Definitions for core predictors associated with risk of adverse COVID-19 outcomes

Predictor	Definition
Age	A continuous measure of age (in years) at the index date (1 February 2020), calculated using date of birth as recorded in HR or professional registration databases.
Sex	A categorical measure (female/male/other) as recorded in HR or professional registration databases.
Comorbidities	A categorical measure counting the number of comorbidities for each individual (0, 1 or 2 or more) obtained from primary care records and supplemented with secondary care records in analyses conducted in the hospitalised cohort. Comorbidity count will incorporate conditions from the NHS Digital shielded patient list algorithm and others found to be associated with adverse COVID-19 outcomes.
Socioeconomic deprivation	An ordinal measure using quintiles of the Index of Multiple Deprivation (IMD), the official measure of relative deprivation for small areas in each country, based on residential postcode as recorded in HR or professional registration databases. Where residential postcode is not provided workplace postcode will be used as a surrogate.

HR, human resource; NHS, National Health Service.

Elevated body mass index (BMI), obesity and smoking are also considered key predictors for adverse COVID-19 outcomes;^9 23 24^ however, are likely to be missing for large proportions of the identified cohort. Furthermore, missingness in EHR data is unlikely to be random, preventing standard imputation approaches. Thus, BMI and smoking will not be included as independent predictors in the primary study but instead in a sensitivity analysis exploring COVID-19 outcomes within HCWs where this information is available in primary or secondary care medical records, within 24 months prior to the study start date.

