### Associations between ethnicity, occupation and COVID-19 outcomes

The relationship between ethnicity and COVID-19 outcomes will be assessed using Poisson, logistic and flexible parametric time-to-event regression models (table 3: COVID-19 outcomes and definitions, identified via listed data sources, to be asessed in UK HCW cohort and within listed subgroups, via listed analysis approach in the planned study). For each outcome, multivariable models will incorporate ethnic category and occupational group, and their interactions, adjusted for the four core predictors. The analyses will be conducted by country, and country-specific results combined using meta-analysis methods to produce UK estimates. We will report incidence rate ratios, ORs or HRs with 95% CIs and p-values. Forest plots and cumulative incidence curves will be produced. Interactions between ethnicity and other predictors will be presented graphically to aid interpretation. Model assumptions will be assessed.

We will use directed acyclic graphs to map hypothesised causal associations between ethnicity, occupational group, the core predictors and COVID-19 outcomes. Mediation analysis methods will then be applied to disentangle the direct, indirect and mediated interactive effects of ethnic category and COVID-19 outcomes. The direct effects estimated using the approach are likely to be related to unmeasured explanatory factors, including experiences of structural discrimination and racism, rather than any genetic predispositions for differing outcomes.

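### The BMI and smoking sensitivity analysis changes the covariates and the population together, and no core-adjusted model in the same recorded subset is described

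*Protocol article*

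**What the plan says.** Four places in the protocol article bear on this.

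- **Predictors.** Raised BMI, obesity and smoking are named as key predictors of adverse outcome, but they "are likely to be missing for large proportions of the identified cohort". The section adds that "missingness in EHR data is unlikely to be random, preventing standard imputation approaches". They are therefore kept out of the primary models and used only in a "sensitivity analysis exploring COVID-19 outcomes within HCWs where this information is available in primary or secondary care medical records".
- **Sensitivity and additional analyses.** The operation is given in one line: "adjust for BMI and smoking in COVID-19 outcome models if recorded by EHRs", counting values entered while the study runs or in the 24 months before it. Like the other items in that list, it depends on the numbers of HCWs and events captured.
- **Associations between ethnicity, occupation and COVID-19 outcomes.** The main models are described thus: "multivariable models will incorporate ethnic category and occupational group, and their interactions, adjusted for the four core predictors". This is the only core-adjusted model set out for the broad analysis.
- **Missing data, Baseline characteristics, and Discussion and limitations.** The coverage of each analysis will be reported and missing-data patterns examined. Core predictors will be compared between people with and without recorded ethnicity. The Discussion says sensitivity analyses are meant to account for non-random missingness in ethnicity, BMI and smoking, and accepts that complete-case analysis may introduce sampling bias.

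**The concern.** The article's primary question is whether COVID-19 outcomes differ by ethnicity and occupation among HCWs. The natural use of a BMI and smoking sensitivity analysis is to see whether the ethnicity estimates hold once those predictors are added. The planned analysis takes two steps at once: it adds two covariates, and it drops everyone without a record. By the article's own account those dropped are numerous and not a random sample.

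If the ethnicity ratio is lower in this analysis than in the main model, there are two possible reasons. BMI and smoking may carry part of the difference, or people with recorded values (plausibly those with more healthcare contact) may have a different ethnicity ratio to begin with. If the ratio is unchanged, the two influences may have cancelled. The planned output cannot tell these apart. The article says its findings will inform guidance on health inequalities, and this is its only described analysis of the two predictors.

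**Working it through.** **Reading check.** The article attaches no figure to this analysis, so there is none to reproduce. The structural point can be read from the text:

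| Model described | Covariates | Population |
|---|---|---|
| Main model | Ethnicity, occupation, their interactions, four core predictors | Main cohort |
| Sensitivity model | The same plus BMI and smoking | HCWs with BMI and smoking recorded |
| Core model in the recorded subset | – | Not described |

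The two described models differ in both columns. Separating the two influences needs the third row. Coverage reporting shows how far the population shrinks, but not what that does to the ethnicity estimate. The recorded-versus-missing comparison in Baseline characteristics concerns ethnicity only. The multiple-imputation item names no variables, and Predictors says standard imputation is prevented for these data.

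**Can selection alone move the estimate?** All inputs here are assumed, because the article gives none. BMI and smoking are given no effect at all.

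- Comorbidity: 30% of HCWs, with baseline risk 1.35 times that of the other 70%.
- Ethnicity IRR without and with comorbidity: 1.8 and 1.3, or in a milder version 1.6 and 1.4.
- Probability of recording without and with comorbidity: 25% and 75%, or 30% and 60%.
- Within a comorbidity stratum, recording does not depend on ethnicity or outcome.

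A model with no ethnicity-by-comorbidity term returns approximately an event-weighted average:

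ln(IRR) = Σ w·ln(IRR in stratum) / Σ w, where w = share × relative baseline risk × recording probability (set to 1 for the full cohort).

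Stratum IRRs 1.8 and 1.3 (logs 0.5878 and 0.2624):

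- Full cohort: weights 0.700 and 0.30 × 1.35 = 0.405. (0.700 × 0.5878 + 0.405 × 0.2624) / 1.105 = 0.4685, so IRR 1.598.
- Recording 25%/75%: weights 0.175 and 0.30375. The average is 0.3813, so IRR 1.464. Fall in log IRR: 1 − 0.3813/0.4685 = 19%.
- Recording 30%/60%: weights 0.210 and 0.243. The average is 0.4132, so IRR 1.512. Fall: 12%.

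Stratum IRRs 1.6 and 1.4 (logs 0.4700 and 0.3365):

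- Full cohort: 0.4211, so IRR 1.524.
- Recording 25%/75%: 0.3853, so IRR 1.470. Fall: 9% (8.5%).
- Recording 30%/60%: 0.3984, so IRR 1.489. Fall: 5%.

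If the stratum IRRs are equal, the average equals that common value whatever the weights, and the shift is nil.

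A separate set of assumed inputs uses stratum ratios 2.0 and 1.3, baseline risks 2.0% and 3.5%, a 20% minority share, and recording of 40% or 30% against 90%. The ratio moves from 1.68 to 1.55 or 1.50. The result therefore depends on the assumptions, and stronger heterogeneity or more unequal recording can take it slightly past the range above.

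**What the extra model would show.** In the first scenario, the core model fitted in the subset already gives 1.46. Adding BMI and smoking, which have no effect by construction, leaves it at 1.46. The move from 1.60 to 1.46 is then correctly shown as selection, and the contribution of BMI and smoking as zero.

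**The case against.** The strongest reply is that this is silence, not error. The article is a condensed account, the analysis is conditional and secondary, and its wording is compatible with fitting both models in the recorded subset. A fuller analysis plan may do exactly that. This stands in part: the fair statement is that no such model is described, not that it is excluded. The article does, however, specify the subset, the added covariates and a recording window, and the analysis so specified cannot separate the two influences.

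A second reply is that nobody has said the change will be credited to BMI and smoking. That is correct. A reader might infer that the plan means to set the sensitivity estimate only against the full-cohort model and to attribute any movement to the two predictors. The documents say neither; Predictors speaks only of exploring outcomes.

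Third, the illustration needs effect modification. Comorbidity is already a core adjuster, so unequal recording by comorbidity does nothing unless the ethnicity effect itself differs by comorbidity. This stands in full. The article also plans to graph interactions between ethnicity and other predictors, which might reveal such heterogeneity.

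Fourth, much larger distortions can be produced if recording depends on becoming a case. With an assumed baseline risk of 2.29% (the article's 32 042 expected cases in 1.4 million), a true ratio of 1.50, recording of 80% in cases and 50%/70% in White/minority non-cases, the ratio becomes 1.08. With 50%/40% in non-cases it becomes 1.84. A reader might take these as the size of the problem here. They are not, because they require outcome-dependent recording, chiefly from values entered during follow-up. Sensitivity and additional analyses admits such values, while Predictors admits only those "within 24 months prior to the study start date". The two sections must be reconciled, but that is a separate matter and the present point holds under either window.

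**Conclusion.** The concern holds in limited form. As described, the analysis adds two covariates and restricts to a subset the article itself regards as non-randomly recorded, with no core-adjusted model in that subset. A difference from the main estimate would therefore mix selection with covariate adjustment, and agreement would not rule out either.

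The size of the selection part is unknown. The 5% to 19% fall in the log IRR comes from four scenarios with assumed effect modification by comorbidity and assumed differential recording. It is nil by this mechanism if the ethnicity effect is the same across comorbidity. It should not be read as an estimate of bias in this study.

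A reader might extend the point to the nested ethnicity, occupation and exposure models of the HR sub-study. The article does not support that, since it does not say those added predictors will be largely or selectively incomplete.

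This is an inexpensive improvement to a secondary analysis. It does not affect the main results.

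**What to change.** Add a sentence to the BMI and smoking item in Sensitivity and additional analyses, to this effect: among HCWs with both BMI and smoking recorded, the core model (ethnicity, occupation, their interactions and the four core predictors) will be fitted first, and then the same model plus BMI and smoking. The contribution of BMI and smoking will be judged only from the change between these two fits. The core model in the subset will be set against the core model in the full cohort and reported as the selection effect.

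The cost is one extra model per outcome on data already held, and one more column in the results table. No stated figure in the article changes.

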## Methods

### Study design

We will use data from multiple linked electronic health record (EHR) databases to investigate the study hypotheses within a cohort of HCWs. The cohort study will begin on 1 February 2020 (date following first confirmed COVID-19 case in UK) and follow participants for 1 year, until 31 January 2021.

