### Main exposures

The main exposure of interest is ethnicity, which is likely to be inconsistently recorded across databases. We will primarily assign ethnicity using staff HR records (ESR or SWISS) and registration databases (if not included/missing from HR records). If ethnicity is missing from these databases, linked EHRs will be assessed. Those with ethnicity recorded as ‘not stated’ or with completely missing ethnicity information will be excluded from the main analyses. Ethnicity will be categorised based on ONS groupings (table 2).

**Table 2 T2:** ONS ethnicity groupings

Broad ethnic categories	Ethnic groups
White	English/Welsh/Scottish/Northern Irish/British Irish Gypsy or Irish Traveller Any other White background
Mixed/multiple ethnic groups	White and Black Caribbean White and Black African White and Asian Any other mixed/multiple ethnic background
Asian/Asian British	Indian Pakistani Bangladeshi Chinese Any other Asian background
Black/African/Caribbean/Black British	African Caribbean Any other Black/African/Caribbean background
Other ethnic group	Arab Any other ethnic group

ONS, Office for National Statistics.

A more granular analysis will incorporate subdivisions of ethnicity (particularly within Asian/Asian British category) if a sufficient number of events are observed.

Occupational group (and its interaction with ethnicity) is also of primary interest. We will assign occupation for the main cohort using data recorded on 1 February 2020 from either HR records or data held by the regulating bodies and the following categories informed by version 17.1 of the NHS Occupational Code Manual (*NHS Digital*):

Ambulance staffAdministrations and estates staffHealthcare assistants and other support staffMedical staffDental staffNursing, midwifery and health visiting staffNursing, midwifery and health visiting learnersScientific, therapeutic and technical staffHealthcare sciencesGeneral payments

A more granular analysis will incorporate subdivisions of occupational groups (particularly the Medical staff group) if a sufficient number of events are observed.

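### The protocol gives two conflicting recording windows for BMI and smoking in the same sensitivity analysis, and one of them runs through the outcome year

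*Protocol article*

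**What the plan says.** The Predictors section names BMI, obesity and smoking as key predictors but leaves BMI and smoking out of the primary models, because they "are likely to be missing for large proportions of the identified cohort" and because "missingness in EHR data is unlikely to be random, preventing standard imputation approaches". They move to a sensitivity analysis confined to workers for whom the information is "available in primary or secondary care medical records, within 24 months prior to the study start date".

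The Sensitivity and additional analyses section describes the same adjustment, within the broad analysis, and uses BMI and smoking "if recorded by EHRs either during, or in the 24 months prior to, the study period". That list of analyses is conditional on how many workers and events are captured.

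The Study design section starts the cohort on 1 February 2020 and will "follow participants for 1 year, until 31 January 2021". Table 3 defines the outcomes as events within that same period.

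For ethnicity, the Main exposures section sets one order of sources: staff human resources records, then professional registers, then health records. The last step reads "If ethnicity is missing from these databases, linked EHRs will be assessed", with no date limit. Workers whose ethnicity is still unknown are left out of the main analyses.

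**The concern.** Both windows are stated and only one can be followed. The wider one sits under the statistical analysis plan heading, where an analyst would look first.

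The difference matters because having a record decides who is analysed. A window that closes before follow-up cannot let a later outcome decide entry. A window that stays open through follow-up can: a hospital contact during the year may create the BMI or smoking entry that admits the worker, and hospital contact is itself one of the outcomes. A value taken during or after illness may also differ from the value before it, so the covariate could be a consequence of the outcome.

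This is the only place where the protocol plans to adjust for BMI and smoking. Its purpose is to show whether the ethnicity associations survive that adjustment. A check that selects on the outcome could reassure or alarm wrongly. The Discussion itself warns of collider bias from non-random sampling.

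**Working it through.** **Text comparison**

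| | Predictors | Sensitivity and additional analyses |
|---|---|---|
| Opens | 24 months before study start | 24 months before the study period |
| Closes | study start, 1 February 2020 | end of study period, 31 January 2021 |
| Overlap with outcome period | none | all 12 months |

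No other section chooses between them. The protocol states no numerical result on this point, so there is no figure to reproduce.

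**Illustration of size.** All rates here are assumptions; the protocol gives none. Let p be the share of a group with a value recorded before study start. Among the rest, let r1 be the share of hospitalised workers, and r0 the share of other workers, who gain a value during follow-up. The share entering the analysis is

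S(r) = p + (1 − p) × r.

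The apparent odds of the event within a group are multiplied by S(r1)/S(r0). The ethnicity odds ratio is multiplied by the minority-group ratio divided by the White ratio. In these scenarios r1 and r0 are the same in both ethnic groups and only p differs.

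With r1 = 0.80 and r0 = 0.15:

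- p = 0.50: S(r1) = 0.50 + 0.50 × 0.80 = 0.900; S(r0) = 0.50 + 0.50 × 0.15 = 0.575; ratio 1.57.
- p = 0.40: 0.880 / 0.490 = 1.80.
- p = 0.30: 0.860 / 0.405 = 2.12.

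| p, White | p, minority | Factor on the ethnicity odds ratio |
|---|---|---|
| 0.50 | 0.50 | 1.00 |
| 0.50 | 0.40 | 1.15 |
| 0.50 | 0.30 | 1.36 |
| 0.30 | 0.50 | 0.74 |

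The widest scenario uses r1 = 0.90 and r0 = 0.10. For p = 0.30 the ratio is 0.93/0.37 = 2.51; for p = 0.50 it is 0.95/0.55 = 1.73. The factor is then 2.51/1.73 = 1.46 with the minority group less well recorded, and 0.69 with the groups reversed. Over all scenarios tried with r1 above r0 (p of 0.30 to 0.50), the within-group odds rise 1.13 to 2.51-fold.

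**Window closed at study start.** Here r1 = r0 = 0, so S = p for cases and non-cases alike, and every factor above becomes 1.00. This removes selection through recording after study start. It does not make recording before study start random.

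**Ethnicity fallback.** With a share m missing from staff and register data, the share retained is (1 − m) + m × r. For m of 5% to 20%, and r1/r0 of 0.50/0.15, 0.80/0.15 or 0.90/0.50, risk is inflated 1.02 to 1.16-fold. If m differs by group (5% v 10%, 5% v 20%, 10% v 20%, with the last two r1/r0 pairs), the odds ratio is multiplied by about 1.02 to 1.12. These rates are also assumed.

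**The case against.** The strongest reply is about reach. BMI and smoking are kept out of the primary models, and the analysis that uses them is conditional on numbers. The contradiction therefore touches no main estimate. This stands, and it limits the severity.

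The second reply is about mechanism. The protocol does not say that BMI or smoking is recorded preferentially at COVID-19 admission; it says only that missingness is not random. Selection on outcome alone inflates rates in the subset but leaves the ethnicity odds ratio unchanged, as the 0.50/0.50 row shows. This also stands. Distortion of the odds ratio needs recording to depend jointly on outcome and ethnicity, which is plausible but not documented.

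A reader might infer that the ethnicity fallback has the same flaw. The document does not support that. There is one rule and no conflict, it is the third source in order, and illness does not alter ethnicity. The linked records include primary care, so a worker without the outcome can be recovered too. The protocol also plans to compare workers with and without recorded ethnicity, plans work on missing ethnicity, and admits possible bias from complete-case analysis. What is left is that recovery may depend on contact with care during follow-up.

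A reader might extend the point to comorbidity, which Table 4 says is "supplemented with secondary care records in analyses conducted in the hospitalised cohort". That does not follow: everyone in that cohort has an admission, and the absence of a code is read as absence of disease, so recording does not decide who is included.

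A reader might also object that a subset result will be compared with the full-cohort model. The article does not say how the comparison will be made, and that detail can properly sit in a fuller plan.

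**Conclusion.** The point holds in a limited form. Two sections set different windows for one analysis, and the wider one covers the whole outcome period. Following it would let both inclusion and the covariate value depend on the outcome.

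The contradiction rests on the text alone. The size rests on assumed recording rates. If cases are recorded more often, event rates in the subset are too high. The ethnicity odds ratio is off by roughly 0.7 to 1.5 in the scenarios where pre-start recording differs between ethnic groups, and by nothing where recording is equal across them. It should be corrected, but it does not threaten the main analyses.

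The undated ethnicity fallback is a separate, minor weakness. It does bear on the main analysis, but with a smaller illustrative effect.

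**What to change.** In Sensitivity and additional analyses, state the window already given under Predictors: BMI and smoking values recorded in primary or secondary care in the 24 months before 1 February 2020, with nothing recorded on or after that date. This is one sentence. The cost is fewer workers with BMI or smoking data; the protocol gives no percentages from which to estimate how many.

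For ethnicity, add one check that accepts health-record ethnicity only if it was recorded before 1 February 2020, and report whether the main estimates change. The cost is one further run and a smaller sample in that check; the main source order can stay as it is.

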## Statistical analysis plan

### Statistical principles

Reporting will be in line with Strengthening The Reporting of OBservational studies in Epidemiology (STROBE)^25^ and REporting of studies Conducted using Observational Routinely collected health Data^26^ guidelines. Any dissemination of study findings will follow best-practice guidelines for deductive disclosure. Only aggregate data will be included in publications, 95% CIs will be reported throughout and p-values<0.05 will indicate statistical significance. Multiple testing adjustments will not be made but emphasis will be on effect size rather than statistical significance. Deviations to this protocol and analysis plan will be outlined with justification in the final reporting of the results.

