### HR sub-study

We will conduct the analysis separately for all countries where both HR and outcomes data are available, country-specific results will be presented.

Each outcome will be evaluated using the same regression methods above. Multivariable models will incorporate ethnicity, occupation and the core predictors as before, while extended to incorporate additional predictor information. An ethnicity model will additionally adjust for religion, nationality and country of birth and incorporate their interactions with ethnicity, if appropriate. An occupation model will additionally adjust for primary area of work, role description, patient/non-patient facing, time in current role, place of work, pay grade and seniority. Finally, a COVID-19 exposure model will additionally adjust for absence information and total hours worked as time varying exposures, to assess the impact of changes in COVID-19 exposure over time. Forest plots and cumulative incidence curves will be produced. Interactions between ethnicity and other predictors, and the effects of time varying predictors, will be presented graphically to aid interpretation.

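### The main models make no allowance for clustering by employing organisation, so full-cohort intervals, chiefly for COVID-19 diagnosis, are likely too narrow if infection risk and staff mix both vary between organisations

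*Protocol article*

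**What the plan says.** The section on associations between ethnicity, occupation and COVID-19 outcomes defines the main models: "multivariable models will incorporate ethnic category and occupational group, and their interactions, adjusted for the four core predictors". The only grouping it names is country: "The analyses will be conducted by country, and country-specific results combined using meta-analysis methods to produce UK estimates". It says that model assumptions will be checked, but it names no organisation term, random effect or robust variance.

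Clustering appears under Sensitivity and additional analyses. One item there is to "incorporate clustering of HCWs within organisations by fitting hierarchical models to account for within organisation correlation and between organisation heterogeneity". A second is to "investigate COVID-19 outcomes in hospital workers and cluster HCWs within hospitals using hierarchical models". The list that holds both opens with a condition: "Dependent on the number of HCWs and events captured, we intend to conduct the following additional analyses".

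In the HR sub-study, only the occupation model adjusts for workplace, through covariates that include "patient/non-patient facing, time in current role, place of work, pay grade and seniority". Statistical principles says that "95% CIs will be reported throughout and p-values<0.05 will indicate statistical significance", and also that "emphasis will be on effect size rather than statistical significance".

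**The concern.** Infection can pass between colleagues, and organisations differ in local epidemic intensity. They may also differ in ethnic and occupational mix. Where both risk and mix vary, part of the contrast between ethnic groups reflects which organisations had bad outbreaks. A model that ignores organisation treats that part as if it came from independent people, so its standard error is too small.

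Organisations may hold thousands of staff, so even small correlations can matter. Two things would be at stake. Chance differences between organisations could be read as ethnic or occupational effects. The country-specific standard errors that set the meta-analysis weights would also be wrong. The results are meant to feed into guidance on protecting healthcare workers, so the intervals should be honest.

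**Working it through.** **1. Reproduce the stated infection precision.** Inputs from Sample size: 1.4 million staff; 6.2% infected; White 79.2%, Asian 10.0%, Black 6.1%. Group-specific rates are not given, so I take 6.2% in every group. The 95% half-width for a difference of two independent proportions is 1.96 × √[p(1−p)/n₁ + p(1−p)/n₂], with p(1−p) = 0.062 × 0.938 = 0.05816.

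- White n = 1,108,800; Asian n = 140,000: half-width 0.134 percentage points (stated 0.1%).
- White n = 1,108,800; Black n = 85,400: half-width 0.168 percentage points (stated 0.2%).

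Both match after rounding with no design effect. At these rates, rounding leaves room only for a design effect up to about (0.15/0.134)² = 1.25.

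**2. Choose the design effect.** Ethnicity varies within organisations, so the usual 1 + (m−1) × outcome correlation does not apply. The suitable form is D = 1 + (m−1) × ρx × ρy. Here m is mean organisation size, ρx is the correlation of ethnicity within organisations and ρy that of the outcome. The standard error is understated by a factor of √D. If ρx = 0, then D = 1.

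**3. Diagnosis in the full cohort.** The article gives no organisation count and no correlations. Assumed: 200-300 organisations, ρy 0.001-0.005, ρx 0.05-0.2.

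- Low: m = 1,400,000/300 ≈ 4,667; D = 1 + 4,666 × 0.05 × 0.001 = 1.23; √D = 1.11.
- High: m = 1,400,000/200 = 7,000; D = 1 + 6,999 × 0.2 × 0.005 = 8.00; √D = 2.83.

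The half-widths from step 1 become about 0.15-0.38 points (Asian) and 0.19-0.48 points (Black).

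**4. Simulation check.** Set-up: no true ethnicity effect, 230 equal organisations of 6,087, 2.3% diagnosed (6.2% × 0.37), 10% minority share, 4,000 runs per setting. The last row lies outside the range in step 3.

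| ρy | ρx | True SE / model-based SE | Type I error, model-based | Type I error, cluster-robust |
|---|---|---|---|---|
| 0.001 to 0.01 | 0 | 0.98-0.99 | 4.4-5.2% | 4.8-5.3% |
| 0.001 | 0.05 | 1.14 | 8.2% | 5.5% |
| 0.005 | 0.05 | 1.59 | 21.3% | 5.5% |
| 0.005 | 0.10 | 2.00 | 32.1% | 5.9% |
| 0.01 | 0.10 | 2.65 | 45.3% | 5.9% |

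The formula agrees: at 0.005 and 0.05, D = 1 + 6,086 × 0.00025 = 2.52 and √D = 1.59. With 500 or 100 organisations instead, √D there is 1.30 or 2.12.

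**5. Analyses within confirmed cases.** Sample size expects 32,042 cases, so m is 107 (300 organisations) to 160 (200).

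- Low: D = 1 + 106 × 0.05 × 0.001 = 1.005; √D = 1.00.
- High: D = 1 + 159 × 0.2 × 0.005 = 1.16; √D = 1.08.

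**6. Rarer outcomes in the full cohort.** If the relative variation between organisations (CV) is the same for every outcome, then ρy = CV² × p/(1−p). From ρy = 0.005 at p = 0.023, CV² = 0.005 × 0.977/0.023 = 0.212. For deaths, p = 2,050/1,400,000 = 0.00146, so ρy ≈ 0.0003. At the largest m and ρx, D = 1 + 6,999 × 0.2 × 0.00031 = 1.44 and √D = 1.20.

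**The case against.** The strongest reply is that this is a condensed article. It never says that staff are independent, and the variance estimator is often left to a fuller analysis plan. Clustering is prespecified twice among the additional analyses, and effect size is put ahead of significance. There is also a practical reason to keep organisation out of the main model: the article says that the professional registers hold less information on workplace, and Table 1 lists no staff-record database for Northern Ireland.

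Much of this stands. A reader might infer that the headline intervals are known to be too narrow in every main model. The documents do not support that. They give no correlation or organisation count, there is no inflation if ethnic mix does not vary between organisations, and within confirmed cases the effect is small. Adjustment for deprivation and fitting by country may also remove some of the correlation. A reader might likewise take area of residence as a stand-in cluster for registry-only staff. It does not capture workplace transmission, and coarse areas could be few within a country.

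Three parts of the reply do not stand.

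- The point concerns more than silence: the article states where clustering is handled, and that place is conditional and outside the main models.
- Effect sizes are read with their intervals, so emphasising them does not repair an interval.
- A hierarchical model run alongside leaves the headline intervals as they were. For logistic models it may also estimate a different odds ratio, so it is not a direct check.

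**Conclusion.** The concern holds in a conditional form. As described, the main models allow for no organisation clustering, the plan itself recognises that correlation, and the stated infection precision matches a calculation that assumes independence. Full-cohort intervals, chiefly for diagnosis, are likely too narrow provided that infection risk and ethnic or occupational mix both vary between organisations.

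Under the assumed values, the understatement is a factor of about 1.1-2.8 for diagnosis and about 1.0-1.1 within confirmed cases. For deaths in the full cohort it reaches about 1.2 at the extreme inputs. These figures rest on assumed organisation counts and correlations and on a mean organisation size. Only the ethnicity contrast was calculated; occupation follows the same logic with its own correlation. The true size cannot be derived from the documents.

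**What to change.** 1. In the main models and the HR sub-study, use cluster-robust standard errors on employing organisation for staff with human resource records. The planned hierarchical models already presuppose an organisation identifier.
2. For registry-only staff without an organisation code, report that workplace clustering cannot be accounted for, and do not treat area of residence as an equivalent cluster.
3. Make the organisation-level hierarchical analysis unconditional for staff with human resource records.
4. In Sample size, state that the infection precision assumes independence, or give it with a design-effect range.

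The cost is somewhat wider intervals and slightly changed meta-analysis weights, so pooled estimates may move a little. Point estimates within each country do not change. Some extra work is needed where organisation codes are missing. Where a country has few organisations, plain robust errors can themselves be too small and need a small-sample correction.
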